**Fig. 4 Fig4:**
[figure not shown]
Consort flowchart

#### Sampling for aim 2

To evaluate the implementation outcomes and pathway (Aim 2), 10–15 health care professionals on the alloSCT care team (i.e., senior and assistant physicians, APNs, professional nurses, nurse leaders and management, psychooncologist, nutritionist) will be invited to participate in the focus group interviews. In addition, 10 individual patient interviews will be conducted between June and December 2022 with all participants’ written consent.

### Usual care and intervention group

#### Usual care group (UCG)

Usual care (see context description above) will be given to patients allocated to the UCG*.* If these participants report symptoms or any concerns, the research assistant will encourage them to contact their physicians.

#### Intervention group (IG)

The intervention, i.e., the SMILe-ICM as described above and shown in Fig. 2, will be delivered by eHealth and care coordinators (CCs). The four CCs will be specially-trained APNs. In addition to holding Master’s degrees in nursing, all CCs will be experienced alloSCT experts. Prior to study start, a six-day training segment has been provided by the USB’s SMILe project leader (SV, shared first author) in March 2021. The IG participants will receive care as usual *PLUS* the SMILe-ICM (as described above).

#### Adaptations of the SMILe-ICM intervention to the Swiss setting

The SMILe-ICM was initially developed for the German setting [62], then further developed and adapted to the Swiss setting using information gathered by the contextual analysis [63]. The Swiss adaptations to the SMILe-ICM consisted mainly of technology-based changes to guarantee the SMILe technology’s interoperability with the USB’s information systems and care processes regarding alloSCT patients. A number of adaptions within the Swiss setting’s clinical processes and structures were also necessary. Based on our theoretical framework (the Framework for Reporting Adaptations and Modifications–Expanded (FRAME) [78]), further adaptation required context-specific tailoring of the intervention’s delivery timepoint, and modification both of content (e.g., adding iOS versions of the SMILeApp and EM device, providing less self-management support in the inpatient setting) and of care algorithms based on Swiss clinical requirements.

#### SMILe implementation strategies

Implementation strategies to facilitate the uptake and successful implementation of the SMILe-ICM were contextually tailored to the USB setting by merging our previous experience from University Hospital Freiburg (Germany) [59] with results from the Swiss version’s contextual analysis and adaption phase, which included multiple stakeholders’ perspectives. Following the Expert Recommendations for Implementing Change (ERIC) guidelines [79, 80], we named implementation strategies and reported adaptions using the Framework for Reporting Adaptations and Modifications to Evidence-based Implementation Strategies (FRAME-IS) [81]. In Phase A of the SMILe project, a number of implementation strategies had already been applied and formulated based on the synthesis of the key contextual findings for the first participating centre [59]. As shown in Table 1, further implementation strategies—this time related to the adaption the SMILe-ICM and its evaluation phase—were further elaborated to increase the proposed implementation efforts’ acceptability, appropriateness, and feasibility. Tailoring of implementation strategies were based on multi-stakeholder input and integration of contextual analysis information. As shown in Fig. 5, a bundle of context-specific implementation strategies formulated for the first participating centre (e.g., access new funding, conduct educational meetings) [59], have been further adapted and extended to match the Swiss setting’s adaptation phase A (e.g., develop academic, clinical & technical partnerships, visit other sites, adapt and tailor to Swiss context). For Phase B, specific implementation strategies have been added (e.g., providing clinical supervision, initiating and participating in moderating ongoing consensus discussions, reminding clinicians) and generally guiding the implementation and sustainment phase within the clinical setting.

**Table 1 Tab1:** The SMILe contextually adapted implementation strategy bundlerelated toSMILe project’s phases A and B

Pre-Phase	Phase A	Phase B	Sustainment
**Access new funding**	Conduct local needs assessment and consensus discussion	**Prepare/recruit patients/consumers to be active participants **	
**Develop aca- demic/clinical partnerships**	Develop academic, clinical & technical partnerships	**Ongoing consensus discussion and information of local opinion leaders**	
**Inform local opinion leaders**	**Visit other sites**	**Provide clinical supervision**	
	**Identify early adopters**	**Provide local technical assistance**	
	Organize clinical implementation teams	**Conduct and obtain patients’ and families feedback**	
	**Adapt and tailor to Swiss context**	**Remind clinicians**	
	Develop/adapt educational material	**Spread of clinical innovation**	
	Conduct educational meetings	**Stage implementation scale up**	
	Revise professional roles		
	Create new clinical teams		

***Note.*** Contextually adapted implementation strategies according to ERIC guidelines [79, 80] with respect to SMILe project’s phases A (development & adaption) and B (implementation & evaluation). In bold are those added additionally for the Swiss setting (second participating centre, Phase A and B) from the German setting (first participating centre, Phase A) [59]

**Fig. 5 Fig5:**
[figure not shown]
The SMILe LOGIC model

#### The SMILe ICM’s logic model

In accordance with Smith and colleagues’ “Implementation Research Logic Model” [82], Fig. 5 summarizes the SMILe-ICM in a logic model. While providing information in view of *inputs, activities, outputs, outcomes* and *impact,* this logic model also provides assumptions underlying this complex intervention and highlighting the hypothesised pathways via which we hope the SMILe-ICM and implementation strategies will achieve their intended outputs and outcomes.

#### Data collection and management

Data will be collected at pre-defined time points from April 2021 until March 2024 (T0-Tz, see Table 2) by trained APNs using a standardised method in the IG and by one research assistant (using the same method) in the UCG. SMILe data will be de-identified with access limited only to authorized research study team members.

**Table 2 Tab2:** Variables, measurement and data collection points

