As depicted in Fig. 2 and previously reported [60–62], the SMILe-ICM is based on the five building blocks of the eCCM. It consists of *four modules* (i.e., monitoring & follow-up of vital signs, symptoms and health behaviour; infection prevention; physical activity; medication adherence). Self-management support is driven by behavioural change techniques [64]. The SMILe-ICM relies on two delivery methods: (1) a two-component technology part, i.e., a mobile app for patients (SMILeApp) and its corresponding monitoring interface for care professionals (SMILeCare); and (2) a human part, i.e., APNs acting as *SMILe care coordinators* (CCs).Using the SMILeApp, patients can insert 18 relevant parameters (i.e., vital signs and PROs, see Fig. 2) on a daily basis. All data entered to the SMILeApp will be transferred to the stem cell transplant centre. With each patient’s approval, their input can be overseen by their APN/care coordinators via the SMILeCare monitoring interface. This data transfer allows the APNs to monitor, identify and act upon critical values, symptom-related issues or trends based on pre-established cut-offs and risk-adjusted care protocols. Care protocols also specify when other members of the alloSCT team (e.g., responsible physicians, nurses) will be involved [62]. Patients can also view the progress of their entered values in the SMILeApp and read up on important symptoms in the SMILeApp lexicon. In addition, each patient will receive a step counter to assess his/her daily physical activity. Added for the Swiss setting [63], medication adherence is monitored via the SMILeApp asking for daily intake of immunosuppressive medications and all other ones.In addition, the APNs conduct 12 personal consultations at pre-defined timepoints starting 10 days prior to the patient’s stem cell transplantation and extending to 1 year after. The nursing visits posttransplant are planned in conjunction with the routine outpatient clinic follow-up schedule: first weekly, then monthly for stable patients. During these visits, the APN team provides intervention modules on symptom recognition and assessment, infection prevention, physical activity and medication adherence. For the full first year, considering the patients’ needs, the APNs empower and guide them to self-manage and to support behaviour change, informing and supporting them as necessary based on the course of their disease. As key members of the interdisciplinary team, the APN team promotes productive exchanges between team members and strengthens the role of nursing in the continuum of care.

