#### Randomization process

Intervention patients will receive standard care plus the SMILe-ICM. The usual care group (UCG) will receive standard care. Patients will be randomly allocated 1:1 to the intervention group (IG) or UCG at hospitalisation, i.e., approximately 10 days pre-transplant. Randomization will be stratified by risk group according to age (>/< 65 years), gender (male/female) and living alone (yes/no). The concealed randomization procedure will be implemented via the secuTrial® web-based clinical data management system provided by the USB’s Clinical Trial Unit. After randomization and allocation, no further blinding will be feasible in any group. The study’s duration will be from approximately 10 days pre-transplant to one-year post-transplant, with 3 months’ follow-up after cessation of the intervention period to test for a wane-out effect. A CONSORT flowchart for patients is presented in Fig. 4.

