**Demographics**												
Age	Medical Record, CRF	**X**										
Sex	Medical Record, CRF	**X**										
Education	Questionnaire (4 items)	**X**										
Living alone	Questionnaire (1 item)	**X**										

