The current study includes some risk of contamination bias: while the SMILe–ICM will be tested in an RCT, after the patients are randomised into UCG and IG, they will receive their care from the same alloSCT team. To minimise this risk, the APNs/CCs will only have contact with the IG participants. While this approach will not fully exclude the possibility of contamination, it will reduce it to an acceptable level. Admittedly, a cluster randomised approach would reduce this risk further; yet, given the importance at this stage of the SMILe–ICM’s development of establishing its effectiveness, the RCT design will be adequate.

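### As written, the arm-specific collector rule puts the baseline EQ-5D-5L and PETS after open allocation, and it does not fit a randomisation stratum taken from the same T0a questionnaire

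*Protocol article*

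**What the plan says.** Five statements in the protocol article bear on when, and with whom, the baseline is taken.

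- **Who collects.** Under Data collection and management, "Data will be collected at pre-defined time points from April 2021 until March 2024 (T0-Tz, see Table 2"), and this is done "by trained APNs using a standardised method in the IG and by one research assistant (using the same method) in the UCG". No exception is made for baseline.
- **Who may see whom.** To limit contamination, the Discussion states that "the APNs/CCs will only have contact with the IG participants".
- **When patients are randomised.** The Randomization process section places this "at hospitalisation, i.e., approximately 10 days pre-transplant", stratified by age, gender and living alone. It adds: "After randomization and allocation, no further blinding will be feasible in any group".
- **When the intervention starts.** Under The SMILe-ICM, "the APNs conduct 12 personal consultations at pre-defined timepoints starting 10 days prior to the patient’s stem cell transplantation".
- **What is measured at T0a.** Table 2 sets T0a at day -10. It marks EQ-5D-5L, PETS, education and living alone there (the last two by questionnaire), together with the three implementation scales AIM, IAM and FIM. The next EQ-5D-5L is at day 30 and the next PETS at day 90, both after transplant.

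**The concern.** A baseline for a self-reported outcome should be recorded before the patient knows the arm. If it is not, any reaction to the allocation becomes part of the baseline and cannot afterwards be told apart from a chance imbalance. Here the patient is unblinded, T0a is the only pre-transplant value of both instruments, and in the IG the collector is the person delivering the care model. One of the instruments, PETS, asks directly about treatment burden.

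Health-related quality of life and treatment burden are to be compared between arms over time with mixed models. If T0a enters those models as a time level or as a covariate, a shift in one arm's T0a answers passes wholly or partly into the estimated effect. Its direction cannot be predicted. Disappointment in the usual care group (UCG) or reassurance in the IG would work against the intervention in a change contrast; heightened awareness of burden in the IG would work in its favour.

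**Working it through.** **Step 1: order of events.** The plan gives no figure to reproduce here, so the statements have to be set against each other.

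- All T0 to Tz data in the IG are collected by APNs, and the APNs meet only IG patients. An APN can therefore collect T0a only once the patient is known to be in the IG. Followed literally, T0a comes after allocation.
- The T0a visit also counts as an intervention contact. AIM, IAM and FIM are marked at T0a in Table 2, while the section on implementation outcomes has them completed after a consultation. Table 4 counts face-to-face intervention visits from T0 to T8.
- Living alone must be known before a patient can be randomised within that stratum, yet its listed source in Table 2 is the T0a questionnaire.

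If T0a precedes randomisation, the arm-specific collector rule cannot apply to it. If T0a follows randomisation, the stratum has to come from a source that Table 2 does not name. The passages must be reconciled in either case.

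**Step 2: scale, under assumed values.** The documents give no SD, correlation or shift. Assume 34 evaluable patients per arm (40 × 0.85, using the planned 15% drop-out), a correlation of ρ = 0.5 between T0a and a later visit, no true effect, and a T0a shift of d SD in one arm.

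*Raw change from T0a.* The bias is d in absolute size.
- SE = √(2(1 − ρ)) × √(2/34) = 1 × 0.2425 = 0.243 SD.
- Two-sided error = Φ(−1.96 + d/SE) + Φ(−1.96 − d/SE).
- d = 0.1: d/SE = 0.41, error 0.061 + 0.009 = about 7%.
- d = 0.2: d/SE = 0.82, error 0.128 + 0.003 = about 13%.
- d = 0.3: d/SE = 1.24, error 0.235 + 0.001 = about 24%.

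*T0a as covariate.* The bias is ρd.
- SE = 0.2425 × √(1 − 0.25) = 0.210 SD.
- d = 0.2: bias 0.10, ratio 0.48, error 0.069 + 0.007 = about 8%.
- Over ρ = 0.3 to 0.7, the bias for d = 0.2 runs from 0.06 to 0.14 SD.

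*Comparison.* With 34 per arm, the difference detectable at 80% power is (1.96 + 0.84) × 0.2425 = 0.68 SD, so a 0.2 SD shift is a little under a third of it.

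*QALYs.* By the trapezoid rule (an assumption), T0a carries half of the day -10 to day 30 interval, which is 20 days. That is 20/375 = 5% of the period to day 365, or 20/465 = 4% to day 455. An unadjusted QALY is therefore hardly affected.

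**The case against.** The strongest reply is that the order is inferred. No sentence says that T0a is completed after allocation, and Figures 3 and 4, which may show the sequence, are not available in the text reviewed. The collector sentence is one summary line covering three years, and a condensed article may leave the admission-day routine to the full protocol. The stratum itself suggests that some baseline items are gathered at enrolment, perhaps by the person who screens, with the split between APN and research assistant applying once arms exist. The contamination paragraph in the Discussion also speaks of separation after randomisation.

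This stands as far as it shows that a post-allocation baseline is not proven. It does not remove the point, because on this kinder reading the stated collector rule is wrong for T0a and needs correcting.

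Other parts of the reply also stand:
- Both instruments are patient-completed paper forms, and the PETS looks back four weeks, mostly before admission. This limits the influence of collector and same-day knowledge without removing it.
- The article does not say how T0a enters the models, which may properly be left to the analysis plan. The 7%, 13% and 24% figures apply only to a raw change contrast.
- Table 2 marks AIM, IAM and FIM at 10 time points against 12 consultations, so visits and consultations do not match one to one.

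A reader might infer that the first consultation has contaminated the baseline answers. The documents do not support that: the order within the day -10 visit is not given and the timings are approximate.

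**Conclusion.** The point holds as a conflict in the stated plan. The arm-specific collector rule, combined with the rule that APNs see only IG patients, implies a baseline taken after open allocation. The same rule does not fit a stratum drawn from the T0a questionnaire. An influence of the first consultation on the answers is possible, not shown.

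Exposure is confined to health-related quality of life and treatment burden and, slightly, QALYs. The re-hospitalisation rate is counted from records after the first discharge and does not use T0a, so neither the primary analysis nor the sample size is touched. It would be wrong to read the error rates above as the trial's actual error. They depend on an assumed shift, an assumed correlation of 0.5 and 34 patients per arm. At 0.2 SD they are about 13% for a raw change contrast and about 8% with T0a as covariate. The change is worth making because it is cheap and later analysis cannot reliably separate an allocation effect on T0a from a chance imbalance.

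**What to change.** In Data collection and management and in Table 2, state that:

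- the T0a EQ-5D-5L, PETS, education and living-alone items are completed after written consent and before the allocation is released in secuTrial;
- the same collector takes them for all patients;
- the APN/research assistant split applies from T0b on;
- AIM, IAM and FIM stay after the first consultation.

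For patients already enrolled, record whether T0a came before or after allocation. If the order differed, run a sensitivity analysis, for example a between-arm comparison of the post-transplant visits that does not use T0a. That comparison is unaffected by a T0a shift. Under the assumptions above its SE is √(2/34) = 0.243 SD, against 0.210 SD with T0a as covariate.

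The cost is a change of order on the admission day and about 40 additional sets of baseline forms for the research assistant, which the APNs would otherwise have handled.

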**Primary outcome**												
Re-hospitalisation rate (number of re-hospitalisations per patient year)	FIMA**©** (10 Items) [83] Medical Records, CRF											

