**Secondary Outcomes**		
Healthcare utilization costs	(1) Calculated from the payers’ perspective based on standardised unit costs of resources in Switzerland [84, 85, 91]	EHR
	(2) Medical records and an adapted version of the generic FIMA© self-reporting questionnaire for elderly persons [83]: 7 items, asking retrospectively for number of visits to physicians, days/hours of ambulatory healthcare visits, days/hours of home care services received, days/hours of support by family caregivers, type(s) and duration(s) of rehabilitation therapy, reason(s) and duration(s) of inpatient days (including intensive care unit stays and/or emergency room visits), and current type of insurance.	Paper survey (pat.)
Length re-hospitalizations	(1) The total length of inpatient re-hospitalizations in the first year after alloSCT is the total number of hospitalized days (planned and unplanned) after initial post-alloSCT discharge until end of study, like reported in all medical reports and the generic FIMA© self-reporting questionnaire for elderly persons [83]	Paper survey (pat.) and EHR
Medication adherence (implementation & persistence dimension [67])	(2) Implementation & persistence dimension [67] will be assessed using the Basel Assessment of Adherence to Immunosuppressive Medication Scale (BAASIS©): a validated self-report measure assessing adherence to implementation issues (e.g., drug holidays; 4 items; yes/no) and persistence/discontinuation (1 item; yes/no) [87].	Paper survey (pat.)
	(3) Daily intake (date and time) of immunosuppressive medication will be monitored electronically via the MEMS® Button, [86] which has been indicated previously as the preferred electronic monitoring device [63]. Patients will receive the button shortly before discharge and are instructed on how to use it at home until their immunosuppressants are discontinued. Data will be password-protected and stored on the MEMS® Adherence Software database, which provides an overview of the electronically compiled dosing history per patient [86].	MEMS® Button [86]

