Treatment burden	German version of the PETS© self-reporting questionnaire [88]: nine multi-item domain scales, each measuring the burden of one aspect of chronic illness treatment on a 4- or 5-point Likert-type response scales regarding a 4-week recall time frame: medical information (7 items); medications (7 items); medical appointments (3 items); health monitoring (2 items); interpersonal challenges (4 items); health care expenses (5 items); difficulty with health care services (7 items); role/social activity limitations due to self-management (6 items); and physical/mental exhaustion due to self-management (5 items). Raw domain scores are transformed to a standardised 0-to-100 metric, with higher scores indicating greater treatment burden.	Paper survey (pat.)
Health-related Quality of Life	Measured using the EQ-5D-5L© [89], covering five dimensions (mobility, self-care, usual activities, pain/discomfort and anxiety/depression) and including the EQ–Visual Analogue Scale (VAS), on which individuals rate their overall perceived health state (scale of 0 to 100)	Paper survey (pat.)
Quality-Adjusted Life Year (QALY)	Calculate QALY: Generating these requires the HRQL preference weight (obtained from the EQ-5D-5L© value set for Germany EQ-VT v. 2.0) [92] and time in days between HRQL measurements [93]. QALY scores range from 1 (perfect health) to 0 (dead) [94].	Paper survey (pat.)
GvHD	Incidence and grade of chronic and acute GvHD	EHR
Overall survival rate	Overall survival rate from start of study participation	EHR
Conditioning regimen	Treatments used to prepare a patient for stem cell transplantation (e.g., chemotherapy, monoclonal antibody therapy, and radiation to the entire body)	EHR
Donor match/type	Human leukocyte antigen (HLA) tissue type	EHR
Disease	Primary disease	EHR
If death	Date and cause of death	EHR
If relapse	Date of relapse	EHR

*Abbreviations. BAASIS* Basel Assessment of Adherence to immunosuppressive medication scale. *EHR* Electronic Health Record, *EQ-5D-5L*© European Quality of Life 5 Dimensions 5 Level Version, *EQ-VT* EQ valuation protocol, *GvHD* Graft-versus-Host-Disease, *HRQL* health related quality of life, *pat* patient, *PETS* Patient Experiences with Therapy and Self-management, *QALY* quality-adjusted life years

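### Patient-reported secondary outcomes are collected by the intervention's own nurses in one arm and by a research assistant in the other, so collector and arm cannot be separated

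*Protocol article*

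**What the plan says.** All places are in the protocol article.

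- **Who collects.** Data collection and management says that data at all time points, up to the last follow-up at day 455, are collected "by trained APNs using a standardised method in the IG and by one research assistant (using the same method) in the UCG".
- **Who the APNs are.** Intervention group (IG): "The four CCs will be specially-trained APNs". The SMILe-ICM section adds that "the APNs conduct 12 personal consultations at pre-defined timepoints starting 10 days prior to the patient’s stem cell transplantation and extending to 1 year after", and that at these visits they deliver modules which include medication adherence. With the patient's approval they also see the daily app entries, medication intake among them.
- **No shared collector.** In the Discussion, to limit contamination, "the APNs/CCs will only have contact with the IG participants".
- **Blinding.** Randomization process: "After randomization and allocation, no further blinding will be feasible in any group".
- **Which outcomes are patient-reported.** Table 3 gives a patient paper survey as the source for BAASIS ("a validated self-report measure assessing adherence to implementation issues"), for treatment burden ("German version of the PETS© self-reporting questionnaire"), for the EQ-5D-5L and the QALY derived from it, and, alongside records, for the FIMA items that feed costs and length of re-hospitalisation.
- **Source of the primary outcome.** Table 2 lists FIMA together with "Medical Records, CRF". Table 3 lists only the electronic health record (EHR).

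**The concern.** A patient in the intervention group is asked about missed doses, burden and health by a survey that the nurse coaching them collects. A patient in the usual-care group (UCG) answers the same survey for a research assistant with no stated care role. Under-reporting of missed doses or burden to one's own coordinator is a familiar form of social-desirability bias. Study aims (Aim 1a) predicts lower non-adherence, less burden and better quality of life in the intervention group, which is the direction in which this bias would push.

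The stake is the reading of the secondary effectiveness results. A difference on these surveys could come from the care model, from who collected the form, or from both, and the data would hold nothing to tell them apart. The wane-out comparison in Aim 1b is affected in the same way for BAASIS, EQ-5D-5L and FIMA, which are scheduled at day 455 under the same collection rule. PETS is not scheduled there.

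**Working it through.** No figure in the article is in dispute. The check sets the passages side by side and then sizes the effect under stated assumptions.

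**Step 1: is collector the same variable as arm?** The collectors are APNs in the IG and one research assistant in the UCG (Data collection and management). The APNs have no contact with UCG patients (Discussion). Let A = 1 for IG and 0 for UCG, and C = 1 for an APN collector and 0 for the research assistant. Then C = A for every patient. In a model with mean μ + βA + γC, only β + γ can be estimated. Adding C as a covariate makes the design matrix singular. A larger sample estimates β + γ more precisely but still does not isolate β.

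**Step 2: which outcomes are exposed?**

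| Outcome | Source (Table 3) | Compared between arms | Exposed |
|---|---|---|---|
| BAASIS, PETS, EQ-5D-5L/QALY | patient paper survey | yes | yes |
| Costs, length of re-hospitalisation | records and FIMA | yes | the FIMA part |
| Adherence by MEMS Button | electronic dosing record | yes | largely not |
| GvHD, survival | EHR | yes | largely not |
| Re-hospitalisation rate | EHR (Table 2 adds FIMA) | yes | only if FIMA supplies events |
| AIM, IAM, FIM | surveys of IG patients and coordinators | no | no between-arm confounding |

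**Step 3: how large could it be on a score?** The article gives no collector effect, so a shift of d SD is assumed, with no true treatment effect. For a two-sample comparison of a roughly continuous score at one time point, normal approximation, two-sided α = 0.05, n per arm:

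P(reject) = 1 − Φ(1.96 − m) + Φ(−1.96 − m), with m = d / √(2/n).

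For n = 40 and d = 0.2: √(2/40) = 0.2236 and m = 0.2/0.2236 = 0.894, so P = 1 − Φ(1.066) + Φ(−2.854) = 0.143 + 0.002 = 0.145.

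| Assumed d | n = 40 (recruitment target) | n = 34 (40 less 15% drop-out) | n = 26 (stated minimum) |
|---|---|---|---|
| 0 | 5.0% | 5.0% | 5.0% |
| 0.1 | 7.3% | 7.0% | 6.5% |
| 0.2 | 14.5% | 13.1% | 11.1% |
| 0.3 | 26.9% | 23.6% | 19.1% |

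The excess grows with n, as expected of a bias.

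**Step 4: and on a yes/no item such as BAASIS?** Assume true non-adherence of 30% in both arms, with a fraction w of it withheld in the IG. The apparent odds ratio is [0.30(1−w) / (1 − 0.30(1−w))] / (0.30/0.70). At w = 0 it is 1. At w = 1/3 it is (0.20/0.80)/(0.30/0.70) = 0.58. Values of w between these give odds ratios between 1 and 0.58.

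**The case against.** **The instruments are self-completed, by one standardised method, with trained collectors.** This stands as far as it goes: it removes most interviewer-rating error. It does not change whose patient the respondent is or which collector handles the form. The article does not say that APNs read the forms or sit with the patient. Whether they do may be settled in the full protocol, so the mechanism is plausible but not shown.

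**Adherence is also measured electronically.** This stands and matters. The MEMS Button record does not depend on what a patient tells the nurse, and the Analysis section already names a mixed model for it. It is a real cross-check for BAASIS. There is none for PETS or EQ-5D-5L.

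**The distortion may not reach significance.** Also fair. At one time point with 40 per arm, 20% against 30% gives z = 0.10/√(0.16/40 + 0.21/40) = 1.04, p about 0.30. The estimate is still shifted.

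**Stronger readings to avoid.** A reader might infer that the primary outcome is biased because APNs would hear of outside admissions that go unnoticed in usual care. The documents do not support this. Table 3 gives the EHR alone, eligibility requires follow-up at the transplanting hospital, and usual-care patients are assessed on the same schedule. A reader might also infer that the acceptability, appropriateness and feasibility scores are confounded. They are not compared between arms. Courtesy towards the provider may colour them, but that is a different matter.

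**Conclusion.** The concern holds for the patient-reported secondary outcomes compared between arms: BAASIS, PETS, EQ-5D-5L and its QALY, and the FIMA part of costs and length of stay. That collector coincides with arm follows from what the article states and needs no assumption. The direction of the bias (towards the intervention) is a reasoned expectation, and its size is unknown. The 7% to 27% false-positive range rests on assumed shifts of 0.1 to 0.3 SD, no true effect, 40 per arm and a single time point. MEMS adherence, GvHD and survival are largely outside the problem. The primary outcome is exposed only to the extent that FIMA supplies events, which the mismatch between Tables 2 and 3 leaves open. The Discussion treats the separation of APNs from usual-care patients only as protection against contamination and does not address its effect on outcome assessment. The plan should be changed on this point, though the primary analysis does not stand or fall by it.

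**What to change.** 1. In both arms, have patients complete the paper surveys unaided and return them sealed to the research assistant or the data unit, unseen by the APNs. State this under Data collection and management, and apply it through day 455.
2. Treat the MEMS record as the main adherence measure and BAASIS as supportive.
3. Reconcile Tables 2 and 3 so that re-hospitalisations come from one record-based source, abstracted in the same way in both arms.
4. For surveys already collected under the present arrangement, report who collected them and name this as a limitation.

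**Cost.** Envelopes, a changed hand-over step, and more handling and abstraction time for the existing research assistant, who would take on surveys from the other arm (40 patients at target). The article gives no workload, so whether this fits current hours must be checked. Endpoints and sample size do not change. **What remains.** Patients still know their allocation, so reporting bias from that knowledge stays. The change removes only the part due to the collector.
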